#### 2.8.3. Project Duration and Expected Outcomes

The estimated period of inclusion will be one year. The estimated study completion date will be the end of 2023. The follow-up duration will be one year. The complete duration is estimated to be two years.

The study is expected to demonstrate that both radiotherapy techniques studied avoid the appearance of early- and medium-term perfusion defects. For this purpose, this trial proposes to reinforce the methodology of the previous studies by including a significant number of patients and by performing cardiac SPECT that follows a reversible abnormality detection protocol (resting and stress phases) and is administered at a frequency that covers the other data in the literature.

## 3. Discussion

Breast cancer patients are expected to have a prolonged lifespan, and the potential for a significant cardiovascular event is a significant public health concern. Recent findings indicate that RIHD may arise as an earlier complication and that subclinical cardiac damage can be detected. The conventional irradiation technique for breast cancer is opposite tangential field radiotherapy; however, this technique can cause early perfusional defects, according to the literature. Modern radiotherapy techniques, such as IMRT or DBIH, can result in reduced heart doses and probably do not cause alterations in myocardial perfusion.

## 4. Conclusions

If the hypothesis of the absence of perfusion defects is confirmed, then the benefit of the use of these two irradiation techniques will be real and could be considered as new references.

Cardiac follow-up is regularly questioned after breast radiotherapy; if these techniques show no negative impact, specific post-irradiation monitoring will probably no longer be necessary.

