In patients with left-sided breast cancer, perfusion abnormalities are more commonly observed, indicating that the incidence of these defects is concentrated in the radiotherapy field and is linked to the degree of cardiac exposure [13,14,15]. In a study of 114 patients who received breast cancer irradiation, volume-dependent perfusion defects were detected in approximately 40% of patients within two years after irradiation. The occurrence of new defects was found to be approximately 10% to 20% in patients with less than 5% of their left ventricle included within the irradiation fields and 50% to 60% in those with greater than 5% of their left ventricle included (*p* = 0.33 and *p* < 0.001) [5].

Breast cancer irradiation is mainly achieved by a tangentially opposed field approach. Considering cardiac anatomy, when treating a left breast, it would be expected to have a high dose to the left anterior descending coronary artery (LADA) but not to the left circumflex and right coronary arteries [14,16]. The distribution of the dose to the heart is heterogeneous [17], and cardiac tissues are differently radiosensitive [18,19]. Therefore, MHD may not be the most relevant dose parameter to assess cardiac exposure [20].

In the era of modern radiotherapy techniques, cardiac substructures could be delineated to optimize heart dosimetry and protect patients from cardiac complications [21]. The use of reference atlases and autosegmentation software relevant to these substructures would save time, quality, and reproducibility in delineation and consequently in dose calculation [22,23].

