The correlation between perfusion defects and radiation dose to the myocardium implies that strategies aimed at reducing the radiation dose have the potential to mitigate myocardial damage. The distribution of the radiation dose to the heart is contingent on several factors, including the radiation technique utilized, the irradiated volumes, and the location of the radiation field [24,25]. A variety of radiotherapy techniques are being used to spare the heart [26] by limiting the dose to the heart (intensity-modulated radiotherapy (IMRT), proton therapy) [27], by maneuvers to increase the distance from the heart to the target volume (deep inspiration breath-hold (DIBH), prone position) [28], or by changing the target volume and not including all the breast glandular tissue (partial breast irradiation) [29]. However, since RIHD appears clinically most often many years after irradiation, the clinical impact of these techniques remains uncertain.

The DIBH technique can effectively displace the heart posteriorly, medially, and inferiorly away from the breast and the deep border of the tangential fields. Some investigations have recently been performed to aid in the prediction of major beneficiaries of the DIBH technique using this beam arrangement [30,31], so that non-beneficiaries may be candidates for alternative RT techniques such as IMRT [32]. There is a clear correlation between the incidental radiation of the heart in left breast irradiation and the detection of early postradiotherapy perfusion defects, which highlights the importance of implementing heart sparing techniques. Studies suggest that DIBH may be beneficial in preserving cardiac perfusion, particularly with low cardiac doses of less than 5 Gy at 6 months and 1 year post-radiation therapy [33,34].

Advanced radiotherapy techniques, such as IMRT and VMAT, modify the distribution of doses to the heart by increasing low doses [35,36]. Biophysical models for normal tissue complications suggest that the relationship between radiation dose and heart complications follows a sigmoidal dose-response curve in this case [36], rather than a linear curve. Therefore, the risk of heart complications, which was estimated at 7.4% per Gy by Darby et al. [2], may be overestimated when smaller, more homogeneous doses are used.

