## 2. Materials and Methods

### 2.1. Study Setting

This interventional, nonrandomized, monocentric, descriptive, and prospective pilot study is being led by the University Radiotherapy Department of the Strasbourg-Europe Cancerology Institute (ICANS).

This study was approved by the Ethics Committee of Ouest VI in August 2022 and registered on clinicaltrials.gov in July 2022 (NCT05454553).

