### 2.8. Statistical Analysis

#### 2.8.1. Sample Size

The estimation of the anticipated incidence of perfusion defects is approximately 17%. The two radiotherapy techniques evaluated (DBIH and IMRT) reduce heart exposure to irradiation. The objective of this dose reduction is to reduce the incidence of perfusion defects to 0%. Assuming an α of 0.05 and 80% power, and since two irradiation techniques are evaluated, the study should include at least 58 subjects to ensure adequate power and compensation for possible loss of patients during the protocol (Rosner B. Fundamentals of Biostatistics, 7th ed., Boston, MA: Brooks/Cole).

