## Figures and Tables

**Figure 1 cancers-15-02467-f001:**
[figure not shown]
EDIPE trial schema. Abbreviations: CT: computed tomography; DIBH: deep inspiration breath hold; IMRT: intensity modulated radiation therapy; M: month; RT: radiotherapy; SPECT: single photon emission computed tomography.

**Table 1 cancers-15-02467-t001:** Inclusion and exclusion criteria.

Inclusion Criteria	Exclusion Criteria
Patients with left-sided breast cancer histologically confirmed after lumpectomy or mastectomy with/without lymph node involvement who are planned for DIBH-RT or IMRT Age > 18 years Karnofsky Performance Status > 60% Absence of psychiatric illness hindering follow-up Patient understanding French Signature of informed consent Patient registered with social insurance	Bilateral breast cancer History of thoracic irradiation Pregnancy or breastfeeding Any medical contraindication to cardiac SPECT or chest CT angiography. Any medical contraindications about regadenoson administration Patient under guardianship

Abbreviations: CT: computed tomography; DBIH-RT: deep inspiration breath hold radiotherapy; IMRT: intensity modulated radiotherapy.

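### If no perfusion defects are seen, the article would call the benefit of DIBH and IMRT established, but without a conventional tangential group a zero result shows only a low incidence in this cohort

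*Protocol article*

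**What the plan says.** **Design and population.** Section 2.1 describes "This interventional, nonrandomized, monocentric, descriptive, and prospective pilot study". Table 1 admits patients "who are planned for DIBH-RT or IMRT". No group treated with conventional tangential fields is described.

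**Endpoint and analysis.** The primary endpoint (Section 2.5.1) is the occurrence of perfusion defects on SPECT at 3, 6 and 12 months. An event is a rise in score from the patient's own pre-radiotherapy scan (Sections 2.7.2 and 2.8.2). The tests named in Section 2.8.2 compare time points, correlate SPECT changes with the irradiated heart structures, and relate changes to cardiovascular risk factors. All are internal to the cohort.

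**Reference rate.** Section 2.8.1 states "The estimation of the anticipated incidence of perfusion defects is approximately 17" per cent, with a target of 0%. It gives no source and ties the figure to no technique.

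**The contrast.** The Abstract names opposed tangential fields as the main method, looks for alternatives with less risk, and aims to show that lowering the cardiac dose can prevent defects. The Discussion says: "The conventional irradiation technique for breast cancer is opposite tangential field radiotherapy; however, this technique can cause early perfusional defects, according to the literature".

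**The inference.** Section 2.8.3 expects to demonstrate that both techniques avoid defects. Section 4 adds that, on confirmation, "then the benefit of the use of these two irradiation techniques will be real and could be considered as new references", and then draws a further inference about the need for cardiac monitoring after irradiation.

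**The concern.** A benefit, and a claim to be a new reference, have meaning only against the technique being replaced. The article identifies that technique, but the trial observes nobody treated with it. The rate those patients would have had, with this camera, this scoring rule and this population, is never measured.

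A low or zero incidence could therefore be reported as the causal effect of DIBH and IMRT when other explanations remain open. The article itself points to one. In a series cited in the Introduction, new defects occurred in "approximately 10% to 20% in patients with less than 5% of their left ventricle included within the irradiation fields" and in 50% to 60% of those with more than 5%. Incidence thus depends strongly on how much of the heart is exposed, and patient mix can move it as well as technique. At stake is a conclusion with consequences for practice drawn from a design that can deliver only an incidence.

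**Working it through.** **1. What the sample size implies.** The inputs in Section 2.8.1 are 17% versus 0%, alpha 0.05, 80% power, two techniques and at least 58 subjects. Sidedness and the loss rate are not given, so 58 cannot be derived from these inputs alone.

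- Two-sample comparison, two-sided, pooled variance: n = [1.960·√(2·0.085·0.915) + 0.842·√(0.17·0.83)]² / 0.17² = 41.05, so 42 per arm, 84 in total. One-sided: 33 per arm, 66 in total. With continuity correction: 106 and 88 in total.
- One-sample test against a fixed 17%, with alpha halved for two techniques (0.025, two-sided). The power term vanishes because the variance at 0% is zero: n = (0.83/0.17)·2.241² = 24.5, so 25 per technique, 50 in total. This reaches 58 if loss is 1 − 50/58 = 13.8%.

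None of the two-arm variants tried gives 58. The nearest route is a test of each technique against a constant. So the sizing does not imply a comparator group either.

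**2. What a perfect result would show.** The exact upper 95% limit (two-sided) for zero events is 1 − 0.025^(1/n).

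- n = 58: 1 − 0.025^(1/58) = 6.2%.
- n = 50 evaluable (assumed, since 58 includes an allowance for loss): 1 − 0.025^(1/50) = 7.1%.

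Both limits lie below 17%. The probability of 0/58 if the true rate were 17% is 0.83^58 = 0.00002. A zero result would thus reject 17% as the incidence in this cohort.

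**3. Why that is not a benefit over tangential fields.** Suppose the technique made no difference, so that the cohort had the rate it would have had under conventional treatment. The chance of seeing no events then depends on that unmeasured rate:

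| Assumed conventional rate here | P(0/58) |
|---|---|
| 5% | 0.95^58 = 5.1% |
| 10% | 0.90^58 = 0.2% |
| 17% | 0.83^58 = 0.002% |

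The strength of the conclusion rests on a quantity the trial does not collect. Even where a given rate is clearly excluded, the exclusion does not say why this cohort is lower. The candidates are the technique, patient selection, baseline risk, the CZT camera (Section 2.4) and the event threshold (Section 2.7.2).

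**4. Whether anything in the plan fills the gap.** The baseline scan shows that a defect is new, not what would have happened under another technique. The secondary analyses of risk factors and systemic therapy describe associations within the cohort. The 17% has no stated source or technique. None of these supplies the missing counterfactual.

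**The case against.** The strongest defence is that the operative plan is not comparative. The endpoint is occurrence, the target is 0%, events are changes within patients, and the study calls itself a descriptive pilot. A single-arm pilot is a legitimate choice. The Conclusions are also conditional and tentative, and the sentence quoted from them does not mention tangential fields. Much of this stands: the article does not commit the sponsor to declare superiority whatever happens, and the comparator is inferred from the Abstract and Discussion. It does not remove the point. The expectation to demonstrate avoidance appears in Methods as well as in the outlook, and no other reading gives benefit and new reference a meaning. A fuller analysis plan could not supply patients whom the eligibility criteria leave out.

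Four stronger readings are tempting, and the document does not support them.

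- *Patients are steered to IMRT when DIBH would not help them.* The phrase "so that non-beneficiaries may be candidates for alternative RT techniques such as IMRT" is the Introduction's account of outside investigations, not this trial's allocation rule. Selection is a risk here, not a documented fact.
- *The apparent benefit could be anything from 10 to 70 percentage points.* That range pools unlike quantities: any abnormality after breast irradiation (27 to 70%), a six-month figure (42.9%), and new defects within two years by volume of left ventricle irradiated.
- *Each technique alone would fail to exclude 10%.* This needs an assumed 29/29 split and a two-sided limit. For 0/29 the two-sided limit is 1 − 0.025^(1/29) = 11.9%, but the one-sided limit is 1 − 0.05^(1/29) = 9.8%, and sidedness is not stated. The Abstract also speaks of combining the two techniques, which would make the split meaningless.
- *Other explanations are as likely as the technique.* Nothing in the document ranks them. The point is only that the design cannot tell them apart.

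**Conclusion.** The concern holds as a limit on inference. If no defects are seen, the article would draw a conclusion about benefit that its design cannot support. What 0/58 would support is an incidence in this cohort with an exact two-sided 95% upper limit of 6.2%, or 7.1% if 50 patients were evaluable. Either limit excludes a fixed 17%. It would not establish a difference from conventional tangential radiotherapy of any size.

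This rests on two things: reading benefit and new references as relative to the conventional technique named in the Abstract and Discussion, and the absence of any control group, matched historical cohort or test against an external rate in the article. The choice of a single-arm pilot is not at fault, and recruitment, scans, endpoint and sample size are unaffected. The wording should be corrected before results are reported, because it fixes in advance how they would be read.

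**What to change.** **Sections 2.8.3 and 4.** Replace the claims of demonstrated avoidance and real benefit with text such as: *The study will estimate the incidence of new perfusion defects at 3, 6 and 12 months after DIBH-RT or IMRT, with exact 95% confidence intervals. As there is no control group, a low incidence would be compatible with a benefit over conventional tangential radiotherapy but would not establish it, and would justify a controlled comparison.*

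**Published rates.** Label any comparison with them, including the 17%, as descriptive, and name the series from which each rate comes.

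**Abstract and second sentence of Section 4.** Apply the same limit to the stated aim of showing prevention and to the inference about monitoring after irradiation. The change concerns what this study can support; it takes no position on how patients should be followed.

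**Cost.** Wording only, with no added patients, scans or recalculation. The downside is a less favourable headline claim. For scale, the controlled comparison that the current wording presupposes would need about 42 patients per arm before loss, by the two-sample formula above, if 17% were the conventional rate (an assumption) and the new rate were truly 0%. It would need 59 per arm if the new rate were 2%, and 106 if it were 5%.

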## 5. Patents

Declaration: Ethics approval and consent to participate.

This prospective study was approved by an Ethics Committee (the Committee for the Protection of Persons, CPP) and a competent health authority: the Agence nationale de sécurité du médicament et des produits de santé (ANSM).

## Figures and Tables

**Figure 1 cancers-15-02467-f001:**
[figure not shown]
EDIPE trial schema. Abbreviations: CT: computed tomography; DIBH: deep inspiration breath hold; IMRT: intensity modulated radiation therapy; M: month; RT: radiotherapy; SPECT: single photon emission computed tomography.

**Table 1 cancers-15-02467-t001:** Inclusion and exclusion criteria.

Inclusion Criteria	Exclusion Criteria
Patients with left-sided breast cancer histologically confirmed after lumpectomy or mastectomy with/without lymph node involvement who are planned for DIBH-RT or IMRT Age > 18 years Karnofsky Performance Status > 60% Absence of psychiatric illness hindering follow-up Patient understanding French Signature of informed consent Patient registered with social insurance	Bilateral breast cancer History of thoracic irradiation Pregnancy or breastfeeding Any medical contraindication to cardiac SPECT or chest CT angiography. Any medical contraindications about regadenoson administration Patient under guardianship

Abbreviations: CT: computed tomography; DBIH-RT: deep inspiration breath hold radiotherapy; IMRT: intensity modulated radiotherapy.

## Data Availability

Not applicable.
